## Justification:

To the best of our knowledge, no study has been performed analysing the ploidy state and mtDNA content by PGT-A on IVF/ICSI sibling embryos. Also, no studies are available comparing the developmental kinetics by time lapse imaging between IVF and ICSI embryos within the same patient.

With the overuse of ICSI for non-male factor infertility, this study aims to provide evidence that conventional IVF should be the method of choice.

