### SECONDARY outcome measures (Dependent)

PGT-A:

- mtDNA copy number (de los Santos et al., 2018):
  - Mitoscore value: represents the normalized mtDNA content in (an)euploid embryos and indicates the total mtDNA content in the sample

Pre-implantation development:

- Number of COCs retrieved
- Maturation rate: number of mature oocytes obtained in each arm
  - ICSI: defined on day 0 as the number of injected oocytes/number of COCs assigned to the ICSI group
  - IVF: defined on day 1 as the number of oocytes with an extruded PB/number of inseminated oocytes
- Fertilization rate: number of zygotes with 2PN/number of oocytes assigned to the group
- Embryo quality on day 3 defined by the Istanbul consensus (Alpha Scientists, 2011)
  - The number of blastomeres and their division pattern, fragmentation, presence of compaction, vacuoles, granulation and nuclei will divide the embryos into 3 categories: good, fair or poor
  - Cell number on day 3 for all fertilized oocytes
- Embryo quality on day 5 (Gardner and Schoolcraft,1999) defined by the Istanbul consensus (Alpha Scientists, 2011)
  - The blastulation rate: number of embryos reaching at least the BL1 stage/ number of oocytes assigned to that group: defined by a 1 (yes, the embryo is blastulating) or 0 (no, the embryo is not blastulating)
  - The expansion stage of the blastocyst and the quality of the ICM and TE will divide the embryos into 3 categories according to Istanbul consensus
- Utilization rate: number of embryos that can be used for the patient (=number of embryos that can be biopsied)/number of oocytes assigned to the group
- Day on which the biopsy is performed (day 5,6 or 7)
- Morphokinetic parameters defined by time lapse imaging starting from the time of syngamy/PN fading (Basile et al., 2014)
  - t2: the timing to two cells
  - t3: the timing to three cells
  - t4: the timing to four cells
  - t5: the timing to five cells
  - t8: the timing to eight cells
  - SC: starting to compact
  - M: the timing to morula
  - SB: starting to blastulate
  - B: reaching a BL3 according to Gardner and Schoolcraft, 1999
  - F: reaching a BL4 according to Gardner and Schoolcraft, 1999
  - cc2: t3-t2
  - s2: t4-t3
- Biopsy yes or no: indicating developmental competence or developmental arrest
- Blastocyst gender: male or female

Clinical cycle outcome:

- Pregnancy (yes or no) defined by a βhCG test of > 15IU

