## Sample Size

Considering no study has been performed analyzing the ploidy state, mtDNA content and embryo morphokinetics by PGT-A on IVF/ICSI sibling embryos, we propose a pilot study including 30 couples to assess the feasibility of the study. Moreover, the pilot study will allow us to estimate statistical parameters which enables us to calculate a sample size in a future study in which an acceptable level of power can be established.

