- In order to evaluate morphokinetic parameters defined by time-lapse imaging starting from the time of syngamy and their effect on ploidy, biopsy day, embryo arrest and gender, first we will present a trend chart to describe the average development times of the embryos according to the treatment. Then, growth models (linear or exponential) will be performed for each embryo, to estimate a growth parameter that can be compared between IVF and ICSI treatments.

To compare IVF versus ICSI outcomes in mtDNA:

- A t-test will be used to detect differences in the Mitoscore value depending on the treatment (IVF or ICSI) if we can assume normality distribution for Mitoscore value (in other case, a Wilcoxon test will be performed). Moreover, linear regression models will be performed to analyse the treatment effect in the presence of the remaining covariates.

To compare IVF versus ICSI outcomes in cycle outcomes:

- We will build a contingency table, and then, a chi-squared test will be used in order to compare the pregnancy, biochemical pregnancy, and clinical pregnancy results between IVF versus ICSI treatments. If we found statistical differences, a logistic regression will be performed to evaluate this differences in a model taking into account rest of explanatory variables.
- To compare the implantation rate, a t-test will be used to detect differences in this rate (a Wilcoxon test will be used if we cannot assume normal distribution of data). If we found differences, linear or Poisson regressions will be performed to evaluate them in a model taking into account rest of explanatory variables.

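### The only morphokinetic quantity formally compared between IVF and ICSI is one growth parameter per embryo, which can miss or reverse a delay; the declared timings have no planned between-arm estimate

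*Protocol*

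**What the plan says.** Under Secondary outcome measures, the protocol lists ten times (t2, t3, t4, t5, t8, SC, M, SB, B, F) and two intervals, cc2 = t3-t2 and s2 = t4-t3. Typical entries are "t8: the timing to eight cells" and "B: reaching a BL3 according to Gardner and Schoolcraft, 1999". The clock is fixed there: "Morphokinetic parameters defined by time lapse imaging starting from the time of syngamy/PN fading". Secondary Objectives asks for these parameters to be compared between the two insemination methods.

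The analysis, under Objectives assessment, has two steps. One is a display: "first we will present a trend chart to describe the average development times of the embryos according to the treatment". The other is the comparison: "growth models (linear or exponential) will be performed for each embryo, to estimate a growth parameter", and it is this parameter that is set against the other arm. The protocol does not state the response variable, whether the curve has a free intercept or is fixed at time zero, or how linear and exponential forms are chosen. Exploratory data analysis adds generic summaries of continuous variables (mean, standard deviation, confidence interval), without saying that they are by arm.

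The Justification section gives sibling kinetics as an evidence gap: "no studies are available comparing the developmental kinetics by time lapse imaging between IVF and ICSI embryos within the same patient". Under Sample Size, "we propose a pilot study including 30 couples to assess the feasibility of the study"; the same section says the pilot should supply parameters for sizing a later study, and names embryo morphokinetics among the topics not yet studied.

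**The concern.** The declared outcomes are times in hours. The quantity compared is a slope or rate, which is a different feature of the embryo's course. None of the twelve declared outcomes receives an IVF-ICSI difference, whereas each development rate and quality grade under Objectives assessment has its own comparison.

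A slope or rate summarises the spacing of milestones and discards their location. A difference in location goes into the intercept or scale, which the plan does not compare. A delay at one early milestone can also tilt the fitted curve upwards. So a real difference in the declared outcomes could come out as no difference in the growth parameter, or as a small difference in the opposite direction. The later study would also need differences in hours and their variability, and one composite slope supplies neither.

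**Working it through.** The protocol gives no expected times, spreads, alpha or power for morphokinetics, so there is no figure of its own to reproduce. The check uses algebra, then illustrative fits.

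**1. Constant shift (algebra, no assumed numbers).** Let every time move from t to t' = t + d.
- Linear: N = a + bt = (a - bd) + bt'. The slope b is unchanged.
- Exponential: N = A·exp(kt) = [A·exp(-kd)]·exp(kt'). The rate k is unchanged.

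Only the intercept or scale moves. The same holds for a linear slope on stage rank.

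**2. Illustrative fits.** Assumed hours from pronuclear fading: 2, 3, 4, 5 and 8 cells at 2.5, 13, 14, 26 and 31 h. The mean time is 86.5/5 = 17.3 h. Least squares with a free intercept gives slope = Σ(t - 17.3)(N - 4.4) / Σ(t - 17.3)² = 97.4/511.8 = 0.1903 cells/h. The log-linear exponential rate is 22.93/511.8 = 0.0448 per h.

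| Change to the embryo | Linear slope | Log-linear rate |
|---|---|---|
| All times +1 to +5 h | 0.0% | 0.0% |
| Only t2 +2 h | +6.8% | +5.6% |
| Only t3 and t4 +3 h | +1.3% | +3.6% |
| Only t5 and t8 +2 h | -8.3% | -8.6% |
| All times ×1.05 | -4.8% | -4.8% |
| All times ×1.10 | -9.1% | -9.1% |

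For the t3/t4 row the slope is 92.0/477.0 = 0.1929. There cc2 lengthens from 10.5 to 13.5 h, yet the parameter rises. A non-linear exponential fit gives +14.7% in that row, so the size depends on the fitting method but the direction does not.

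**3. Curve fixed at one cell at time zero.** With the same times, a constant 2 h shift lowers the linear parameter by 8.1% and the exponential one by 7.2%; a 3 h shift lowers them by 11.8% and 10.6%. Anchoring therefore exposes the shift, but the protocol does not state it.

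**4. Late milestones.** SC, M, SB, B and F carry no cell number in the outcome list. If the response is cell number, the curve ends at t8, and no delay confined to SC-F can alter it. If the response is stage rank 1 to 10, it can. With assumed times of 2.5, 13.5, 14, 26, 31, 58, 66, 74, 84 and 92 h, the rank slope is 0.0920. It falls to 0.0770 (-16%) when SC-F are 12 h later and to 0.0658 (-28%) when they are 24 h later.

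**5. Illustrative simulation.** Assumed: 30 couples, 3 embryos per arm, couple SD 1.5 h, embryo SD 2 h, 12% variation in intervals, paired t-test on couple means, two-sided alpha 0.05, 1,000 runs.
- Constant 2 h delay: rejected in 4.6% of runs by the linear slope and 4.9% by the rate (about the false-positive level), against 99.9% by t8.
- Constant 2 h delay with an anchored exponential: about 100%.
- 7% proportional slowing: about 100% by slope and by rate.

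**The case against.** The strongest reply has five parts.

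- **The growth parameter is not blind in general.** Correct. A reader might infer that it gives the same value to any two embryos hours apart. The fits do not support that: proportional slowing, a t5/t8 delay and an anchored curve all move it.
- **Blindness to late delay comes from assuming a cell-count response.** Also correct. The protocol names no response variable, and a stage-rank response does register such a delay. Choices of this kind are often left to the SAP, which is not shown.
- **The trend chart would show a shift.** It would, and the generic summaries may help. But the chart has no stated test or interval, and neither item is a stated IVF-ICSI difference.
- **A uniform delay is a narrow case.** Time zero at pronuclear fading removes earlier offsets, so a uniform delay must arise before t2. Against an assumed t2 of 2.5 h, a 2 h delay is an 80% lengthening (2/2.5). The documents give no evidence on how likely that is. The t2-only and t3/t4-only cases do not need a uniform delay.
- **Other outcomes would pick up large late delays.** Blastulation and day 5 grade are compared between arms, and day of biopsy is a listed outcome. They do not estimate the timings themselves.

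One might also infer that the investigators would read a null growth parameter as proof of equal kinetics. No section says so. What remains is the mismatch between the declared outcomes and the single quantity compared. The protocol itself fixes that method, so an SAP that followed it would inherit the mismatch.

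**Conclusion.** The point holds in a limited form. The one morphokinetic quantity with a planned formal comparison can miss a real difference in the declared outcomes, or show it slightly in the wrong direction, when the curve has a free intercept or scale. For a constant shift the invariance is exact and needs no assumed numbers. For a delay of t2 alone or of t3/t4 alone, the change was between +1.3% and +6.8% for the linear and log-linear fits under the assumed times. Exclusion of SC to F depends on a cell-count response, which the protocol neither states nor rules out. The simulated rejection rates rest on assumed times and spreads and are illustrative only. The declared timings and intervals have no planned between-arm estimate beyond a descriptive chart and generic summaries. This concerns a secondary outcome in a 30-couple pilot, so it is a cheap improvement that should be made; it does not touch the primary comparison.

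**What to change.** Under Objectives assessment, add a direct IVF-ICSI comparison of each of t2, t3, t4, t5, t8, SC, M, SB, B, F, cc2 and s2. Use a mixed model with a couple random effect, and report the difference in hours with a 95% confidence interval, labelled exploratory. One joint model of all milestone times, with milestone, arm and arm-by-milestone terms, is an alternative for the ten times.

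Keep the trend chart. The growth parameter may stay as a secondary summary, provided that one response variable, one anchoring and one model form are stated and used for every embryo; otherwise linear and exponential parameters come in different units (for a cell-count response, cells per hour and per hour).

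The cost is a few lines of text and a standard model on times already annotated. The downside is about twelve correlated estimates in place of one, which the exploratory label should make plain.

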# Abstract

ICSI is commonly used in PGT cases to eliminate any risk of sperm DNA contamination. With the switch from cleavage stage biopsy to biopsy of the full (hatching) blastocyst, this potential risk of contamination can be neglected and could allow the use of conventional IVF in PGT cases. Especially in cases of non-male factor infertility, the use of conventional IVF can be applied as a more ‘natural’ insemination method.

A pilot study will be performed on sibling oocytes including patients with non-male factor infertility and requesting PGT-A (NGS platform). If at least 10 cumulus oocyte complexes (COCs) are obtained after oocyte retrieval, half of the oocytes will be subjected to ICSI and the other half to conventional IVF. Preimplantation development is followed by time lapse imaging and blastocysts (day 5-7) fulfilling the biopsy criteria will undergo trophectoderm biopsy to detect the ploidy state and the mtDNA copy number.

The main objective is to analyse if the use a more physiological insemination method (IVF) has a beneficial impact on the ploidy state of the blastocyst as compared to ICSI within the same patient. As the embryos will be cultured in a time lapse imaging system, annotations can be made and the differences in maturation rate, fertilization rate and embryo development between both insemination methods can be analysed as secondary outcome parameter. On top of this, the PGT-A outcome will also display the mtDNA copy number which can be compared between IVF and ICSI biopsied sibling blastocyst. Euploid blastocysts will be transferred in subsequent FET cycles and give an indication on the clinical outcome between IVF and ICSI.

Would this study enable us to undermine the dogma to perform ICSI for all PGT cycles?

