## Intervention and Follow-up

Couples that are eligible for the study will be selected on the day of OPU based on all inclusion and exclusion criteria (as described under “D. Subject inclusion/exclusion criteria”) and will be asked to participate in the study by signing the IC. A randomization list will determine to which group the first half (or one extra in case an odd number is available) of the oocytes will be assigned. As to prevent selection bias, oocytes will be assigned to both groups under low magnification and different cumulus expansion stages will be evenly divided. Oocytes selected for ICSI will be denuded and injected on the day of OPU after which their pre-implantation development will be followed by time lapse imaging. IVF oocytes will be inseminated (individual or per two) overnight with 10.000 PR sperm cells in a G185 incubator (K systems) and denuded in the morning of day 1 after which they will be transferred to the time lapse imaging incubator. Blastocysts of sufficient quality (to determine this, morphokinetic parameters shall be measured) will be biopsied on day 5-7 after which the blastocysts are vitrified individually. PGT-A (NGS platform) is performed on all TE biopsy samples and the ploidy state and mtDNA score will be provided. All annotated time lapse imaging data will be gathered and combined with the pre-implantation data, PGT-A data (ploidy state and mtDNA copy number) and all general patient and cycle characteristics. Patients with euploid embryos available will receive a FET and implantation rates and (clinical) pregnancy outcomes will be recorded.

The follow-up of the patients does not deviate from a normal fertility trajectory.

Quantification of the determining variables:

The primary outcome variable is the ploidy state

Secondary outcome variables are the (i) embryo development defined by the number of COCs retrieved, maturation and fertilization rate, embryo development analysed on day 3 and day 5, total number of embryos used for the patient, day of biopsy and the morphokinetic parameters; (ii) mtDNA copy number and (iii) the clinical outcome.

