- Biochemical pregnancy (yes or no) defined as a pregnancy in which the hCG levels start do decrease after 1 week
- Implantation rate (%) defined by the number of gestational sacs/number of embryos transferred
- Clinical pregnancy (yes or no) defined by the ultrasonographic visualization of one or more gestational sacs, including ectopic pregnancies

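### The IVF-versus-ICSI tests of pregnancy and implantation compare transfer groups formed after allocation, so a difference could not be attributed to insemination method

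*Protocol*

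**What the plan says.** Under Intervention and Follow-up, allocation applies to oocytes within a couple: "A randomization list will determine to which group the first half" of the oocytes goes. Two selection steps follow. The first is quality: "Blastocysts of sufficient quality (to determine this, morphokinetic parameters shall be measured) will be biopsied on day 5-7". The second is ploidy: "Patients with euploid embryos available will receive a FET and implantation rates and (clinical) pregnancy outcomes will be recorded". The section adds that "The follow-up of the patients does not deviate from a normal fertility trajectory". No section says which arm's embryo is transferred, in what order, or how many at a time.

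Objectives assessment nevertheless fixes formal comparisons by arm. For the three pregnancy outcomes, "a chi-squared test will be used in order to compare the pregnancy, biochemical pregnancy, and clinical pregnancy results between IVF versus ICSI treatments". For implantation, "To compare the implantation rate, a t-test will be used to detect differences in this rate", with a Wilcoxon test if normality cannot be assumed. Regression models with the remaining explanatory variables are run only if a difference is found.

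Implantation is defined as "number of gestational sacs/number of embryos transferred". Fertilisation, blastulation and utilisation are instead defined per oocyte allocated to the arm.

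The Abstract is more modest: "Euploid blastocysts will be transferred in subsequent FET cycles and give an indication on the clinical outcome between IVF and ICSI". Sample Size describes a feasibility pilot of 30 couples and leaves power to a later study.

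**The concern.** The strength of this design is the within-couple split: each couple supplies oocytes to both arms, so couple prognosis is balanced. That protection holds for outcomes counted per allocated oocyte. It is lost at transfer, where a single-embryo transfer places the couple in one arm only, and which arm depends on what survived both selection steps and what was then chosen.

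A p-value from these tests would look like randomised evidence on pregnancy. It could instead reflect differences in the couples and embryos that reached transfer. The risk of over-reading is real, because the Justification section says the study aims to show that conventional IVF should be preferred, and Objectives assessment carries no caveat. A later study that reused this analysis would inherit the problem with more power to reject.

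**Working it through.** The protocol gives no pregnancy rate, power, alpha or euploid yield, so there is no figure of its own to reproduce. Only the 30 couples and the list of explanatory variables come from the document. The other inputs are assumptions.

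**1. Who enters each transfer group.**
- Oocytes: allocated by the randomisation list, both arms within each couple.
- Biopsied blastocysts: selected on quality after allocation.
- Transferable embryos: selected on euploidy after biopsy.
- Transferred embryo: chosen under usual care, with no rule by arm.

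A couple with euploid embryos from one arm only can appear only in that arm, and a couple with none does not appear. With one single-embryo transfer per couple, no couple appears in both arms, so the comparison is between couples.

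**2. What this can do to the test.** A simulation (400 runs per setting) was built on these assumptions: on average about one euploid blastocyst per arm per couple; couple prognosis normal with SD 1; one transfer per couple; logit of pregnancy = 0.2 + prognosis + 0.8 × embryo quality; chi-squared without continuity correction at two-sided 5%. About 26 of 30 couples reached transfer. The best-quality embryo was transferred unless stated otherwise.

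| Setting | Mean IVF − ICSI difference, 30 / 300 couples | Rejection, 30 / 300 couples |
|---|---|---|
| Insemination affects nothing, choice blind to arm | 1.6 / −0.3 points | 5.8% / 4.8% |
| As above, but IVF embryo taken only if clearly better | 1.8 / 1.3 points | 5.0% / 5.5% |
| No effect on a transferred embryo's potential, but IVF euploid yield multiplied by exp(0.7 × prognosis) | 13.0 / 12.2 points | 9.5% / 54.5% |
| Real IVF quality advantage of 0.5 SD | 8.0 / 5.8 points | 9.0% / 17.5% |

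The first two rows show that post-allocation choice does not by itself break the test. The third shows a difference of 12 to 13 points produced only by which couples supply IVF embryos. In this model that exceeds the difference from a real quality advantage (fourth row), and the test cannot tell the two apart.

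**3. Precision.** Half-width = 1.96 × √[p(1−p)(1/n₁ + 1/n₂)], with p = 0.5:
- 10 v 10: 1.96 × √(0.25 × 0.2000) = 0.438
- 12 v 13: 1.96 × √(0.25 × 0.1603) = 0.392
- 15 v 15: 1.96 × √(0.25 × 0.1333) = 0.358

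So 20 to 30 first transfers give about ±36 to ±44 points.

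**4. Expected counts.** At 50% pregnancy: 0.5 × 10 = 5.0 to 0.5 × 15 = 7.5 per cell. At an assumed 10% biochemical rate: 0.10 × 10 = 1.0 to 0.10 × 15 = 1.5 events per arm. Only the biochemical outcome falls below 5.

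**5. Follow-up models.** The explanatory variables section lists four sperm values (concentration and progressive motility, before and after capacitation) and 16 other characteristics: 4 + 16 = 20, besides the intervention. There are at most about 30 first transfers. Such a model is close to saturated, is run only after a significant result, and does not include the embryo-level selection.

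**The case against.** The strongest reply is that clinical outcome is the last-listed secondary outcome of a feasibility pilot, that the Abstract promises only an indication, and that low power is already conceded under Sample Size. That is fair, and it limits the severity. It does not remove the point, because Objectives assessment prescribes tests without saying that the comparison is observational.

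Several stronger readings are tempting, and the protocol does not support them.
- **The tests cannot show anything, or are invalid.** A reader might infer this, but they keep their size when insemination affects nothing and choice is blind to arm. The inflated setting rests on a link between IVF yield and prognosis that has no source in the protocol. At 30 couples its 9.5% has a Monte Carlo interval of 0.095 ± 1.96 × √(0.095 × 0.905/400), about 6.6% to 12.4%. The 54.5% belongs to a study ten times larger.
- **Cell counts are too small for chi-squared throughout.** Under the assumptions above this is true only of biochemical pregnancy.
- **A t-test will be run on 0/1 implantation data.** The protocol provides a Wilcoxon fallback.
- **Repeat or mixed-origin transfers will be pooled as independent rows.** The protocol neither states nor rules out either kind of transfer. If a couple contributes more than one, the tests as written would treat the rows as independent. A separate analysis plan might settle this, so it is secondary here.

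The interval widths measure imprecision. They do not estimate selection bias, whose size cannot be derived from the protocol.

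**Conclusion.** The point holds in a limited form. Allocation covers oocytes only; the pregnancy and implantation tests compare transfer groups formed after allocation and largely between couples. A difference could not be attributed to insemination method, and the conditional regressions do not restore that attribution. This follows from the text and needs no assumed rates.

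The numerical size does rest on assumptions: about ±36 to ±44 points for the 95% CI with 20 to 30 first transfers, an even split and 50% pregnancy. The 12 to 13 point difference illustrates what selection could do under one invented mechanism and is not a prediction for this trial.

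Severity is minor to moderate. A reader might infer that the ploidy comparison is undermined too, but it is made before any transfer and is untouched by this point.

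**What to change.** In Objectives assessment, replace the IVF-versus-ICSI tests and follow-up regressions for cycle outcomes with descriptive reporting:
- Tabulate pregnancy, biochemical pregnancy, clinical pregnancy and implantation by arm of origin of the transferred embryo, as counts with exact 95% CIs.
- Base the table on each couple's first single-embryo transfer. List any later or mixed-origin transfers separately.
- State that the transferred embryo was not randomised and that the comparison is observational, in line with the Abstract.

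If the sponsor prefers to keep the tests, the lighter alternative is to describe how the transferred embryo comes to be chosen, label the comparison observational, and say how transfers with embryos from both arms are classified.

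The cost of the main fix is wording and the loss of p-values for clinical outcomes. Nothing changes in patient care, data collection or the primary analysis.
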